## Abstract

**Introduction:**

Radiotherapy is the most common curative treatment for non-metastatic prostate cancer; however, up to 13% of patients will develop local recurrence within 10 years. Patients can undergo further and potentially curative treatment including salvage surgery, brachytherapy (BT), external beam radiotherapy, high-intensity focused ultrasound and cryotherapy. Systematic review shows that high-dose-rate (HDR) BT and stereotactic body radiotherapy (SBRT) have the best outcomes in terms of biochemical control and lowest side effects. The reirradiation options for previously irradiated prostate cancer (RO-PIP) trial aims to determine the feasibility of recruitment to a trial randomising patients to salvage HDR-BT or SBRT and provide prospective data on patient recorded toxicity outcomes that will inform a future phase III trial.

**Methods and analysis:**

The primary endpoint of the RO-PIP feasibility study is to evaluate the patient recruitment potential over 2 years to a trial randomising to either SBRT or HDR-BT for patients who develop local recurrence of prostate cancer following previous radiation therapy. The aim is to recruit 60 patients across 3 sites over 2 years and randomise 1:1 to SBRT or HDR-BT. Secondary objectives include recording clinician and patient-reported outcome measures to evaluate treatment-related toxicity. In addition, the study aims to identify potential imaging, genomic and proteomic biomarkers that are predictive of toxicity and outcome based on hypoxia status, a prognostic marker of prostate cancer.

**Ethics and dissemination:**

This study has been approved by the Yorkshire and The Humber—Bradford Leeds Research Ethics Committee (Reference: 21/YH/0305, IRAS: 297060, January 2022). The results will be presented in national and international conferences, published in peer-reviewed journals and will be communicated to relevant stakeholders. A plain English report will be shared with the study participants, patients’ organisations and media.

**Trial registration number:**

ISRCTN 12238218 ([name] NIHR CPMS Team).

Strengths and limitations of this studyThe reirradiation options for previously irradiated prostate cancer study is the first to assess the feasibility to randomise men to different salvage radiation treatments for radio-recurrent prostate cancer.Randomised radiation treatment allocation will prevent selection bias.Using patient-reported outcome measures to collect treatment toxicity, data will allow for more patient-centred care.The addition of translational components into study will reveal information on the systemic and local effect of prostate reirradiation and identify candidate radioresponse biomarkers for inclusion in a phase III trial.Due to the feasibility design of the study, it is not powered to assess for differences in outcome between stereotactic body radiotherapy and high-dose-rate brachytherapy.

## Introduction

Prostate cancer is the most common cancer in men in the UK with approximately 48 500 new diagnoses every year and this has increased over the last 10 years.^1^ Worldwide, prostate cancer accounts for over 1.2 million new cases and causes over 350 000 deaths (3.8% of all deaths caused by cancer in men) annually.^2^ Radiation therapy (RT) is the most common curative treatment for non-metastatic prostate cancer.^3 4^ Despite advances in diagnostic imaging, RT delivery techniques and dose-escalation strategies, treatment failure remains common.^5–7^ At 10 years, the biochemical failure rate following treatment for localised prostate cancer with RT alone is 41%.^8^ Following dose-escalated RT, the most common site of cancer recurrence is in the prostate with 11-year cumulative incidence of local recurrence 7.2% and 13% in intermediate, and high-risk National Comprehensive Cancer Network prostate cancer groups, respectively.^7^

Multiple salvage options are available for locally recurrent disease including prostatectomy, reirradiation (with brachytherapy (BT) or external beam radiotherapy (EBRT)) and other focal therapies such as high-intensity focused ultrasound and cryotherapy. The evidence on the long-term effectiveness and quality-of-life impact for these treatments is limited; however, reirradiation techniques are the safest and most effective out of the currently available salvage treatment options.^9–13^ Most of the published literature describes retrospective case series with heterogeneous methodologies and radiation treatment techniques with no high-level evidence for the superiority of any of the reirradiation approaches or prospective comparative studies. Only a small proportion of patients with locally recurrent prostate cancer following primary radiotherapy (15%–20%) undergo local salvage therapy according to the Cancer of the Prostate Strategic Urologic Research Endeavor Registry.^14^

Prostate BT involves the placement of sealed radiation sources into the prostate and offers the ability to deliver highly conformal high-dose radiation with a steep dose gradient and rapid fall off in dose, which minimises radiation toxicity to surrounding organs at risk, specifically the rectum and bladder.^15^ Advances in image-guided-targeted BT may allow for more precise and focused treatments.^16–18^ BT can be delivered either via a permanent low-dose rate seed implant (LDR-BT), or via high-dose-rate BT (HDR-BT), which uses a high-activity radiation source (eg, iridium-192) that is temporarily introduced into applicators that are placed within the prostate, typically over 1–3 fractions. HDR-BT is less susceptible to issues related to prostate oedema and seed migration that might complicate dosimetry following LDR-BT. Current evidence suggests that HDR-BT affords lower toxicity, increased tolerability with similar oncological control compared with LDR-BT.^19^

Previously, salvage EBRT techniques have been associated with higher rates of severe late toxicities and also poor local control.^20^ Stereotactic body radiotherapy (SBRT), involving the delivery of a high dose of radiation to a highly conformal target volume with a steep dose gradient in a small number of fractions, may have benefits. Potential advantages include increased sparing of normal tissues than other types of EBRT and being less invasive compared with BT.^21^ BT is also highly specialised and only available in specialist centres.

A prospective trial is required to describe the toxicity profiles for these two most promising options, HDR-BT and SBRT, to allow clinicians and patients to make an informed decision on the most appropriate salvage treatment choice and help inform a larger study with an efficacy endpoint. Strategies to personalise salvage treatment through finding predictive genomic and imaging biomarkers are also required to optimise treatment outcomes.

The reirradiation options for previously irradiated prostate cancer (RO-PIP) trial is the first prospective randomised trial to determine the feasibility of recruitment to a trial comparing SBRT and HDR-BT for locally recurrent prostate cancer and inform power calculations for a definitive randomised control trial (RCT). In addition, this feasibility trial will also quantify the impact on patient-reported outcome measures (PROMs), quantify longitudinal functional MRI changes and assess proteomic, immune and genomic biomarkers.

## Method

### Study design

The Standard Protocol Items: Recommendations for Interventional Trials (SPIRIT) checklist was adhered to when drafting the RO-PIP protocol.^22^ A completed SPIRIT checklist can be found with the trial protocol submission. A schematic overview of the study is shown in figure 1.

**Figure 1 F1:**
[figure not shown]
Schematic overview of study. CTCAE, Common Terminology Criteria for Adverse Events; EORTC QLQ, European Organization for the Research and Treatment of Cancer Quality of Life Questionnaire; EPIC, Expanded Prostate Cancer Index Composite; IPSS, International Prostate Symptom Score; mpMRI, multiparametric MRI; PET, positron emission tomography; QoL, quality of life.

### Study setting

The planned study is a prospective two arm (HDR-BT and SBRT) randomised (1:1) feasibility trial aiming to recruit a total of 60 patients with locally recurrent prostate cancer across three tertiary referral oncology sites (Christie Hospital NHS Foundation Trust, Leeds Teaching Hospitals NHS Trust and Mount Vernon Cancer Centre, UK). The study will open for recruitment in September 2022, and the estimated primary recruitment completion date is in September 2024 and study completion date in September 2026.

### Patient and public involvement and engagement (PPIE)

We have sought input from the Leeds Cancer PPIE team and Leeds Radiotherapy user group into the protocol design, lay summary and patient information leaflet and have acted on the information provided.

### Consent and withdrawal

All participants will give written informed consent before entering the study and before any assessments or interventions related to the study are undertaken. Consent will be taken by the direct care clinical oncologist or a member of the RO-PIP research team, for example, clinical research fellow or research nurse. Optional consent will be sought for taking extra blood and urine samples for the translational study component. Participants are free to withdraw at any time, or at the discretion of the chief or principal investigator. In the event of withdrawal, any data collected up until that point will be kept and potentially included in any analyses.

### Eligibility criteria

The inclusion criteria are: (1) male individuals aged over 18 years; (2) histologically confirmed locally recurrent prostate cancer (following previous radiotherapy no less than 2 years ago); (3) no metastatic disease; (4) able and willing to provide an informed consent to participate; (5) WHO performance status 0–2; (6) reasonable urinary function (International Prostate Symptom Score (IPSS)<20 and Qmax>10 mL/s on flow tests); (7) greater than 10-year life expectancy.

The exclusion criteria are: (1) patients who are unfit for a general anaesthetic due to other comorbidities; (2) clinical or radiological evidence of metastatic prostate disease; (3) any patient with a medical or psychiatric condition that impairs their ability to give informed consent; (4) contraindication or intolerance of magnetic resonance scanning; (5) prior prostatectomy; (6) history of inflammatory bowel disease.

### Assignment of interventions

Following confirmation of written consent and eligibility, participants will be randomised into the trial by the Leeds Clinical Trials Research Unit (CTRU). Patients will be randomised on a 1:1 basis to receive either HDR-BT or SBRT. Patients will be randomised using stratified permuted blocks, stratified by recruiting site and previous androgen deprivation therapy (ADT) therapy. Randomisation will be performed centrally using the CTRU 9–5 telephone randomisation system. Authorisation codes and personal identification numbers, provided by the CTRU, will be required to access the randomisation system.

### Interventions

#### HDR brachytherapy

Two HDR-BT treatment schedules, either a single fraction 19 Gy treatment or 27 Gy in two fractions approximately 2 weeks apart, will be used to be decided by treating centre.

Gross tumour volume (GTV) will be delineated based on the intraprostatic lesion defined on the multiparametric MRI with or without additional diagnostic PET-CT information; the clinical target volume (CTV) is generated by applying an isotropic 3 mm margin constrained by the urethra (where applicable) and rectum. The CTV and planning target volume (PTV) are considered to be the same structures. The rectum, urethra and bladder should be contoured as organs at risk as per the European Society for Radiotherapy and Oncology (ESTRO) guidelines.^23^

#### Stereotactic body radiotherapy

Patients will receive five fractions of 7.25 Gy per fraction, which will be delivered alternate days over no more than 2 weeks to provide a total dose of 36.25 Gy. Radiotherapy may be delivered using CyberKnife, linear accelerator or MR-linear accelerator. Implanted prostate markers and SpaceOAR may be used as per centre standard of care.

GTV will be delineated based on the intraprostatic lesion defined on the multiparametric MRI with or without additional diagnostic PET-CT information; a CTV will be delineated comprising either the whole prostate or for focal treatment the GTV with a 3 mm margin constrained to the prostate boundaries. The CTV will then be grown by 3–5 mm (dependent on departmental policy and image guidance technique) to generate a PTV. The rectum, bladder, bowel loops (where appropriate) and femoral heads will be contoured as organs at risk.

#### Additional interventions

ADT may be initiated at the discretion of the treating oncologist but this must be started by the time of the first salvage radiotherapy treatment (at first fraction of SBRT or at HDR-BT).

#### Toxicity assessment

Clinician reported treatment toxicity will be summarised at each time point as the proportion of patients experiencing each toxicity, summarised by maximum grade experienced as per Common Terminology Criteria for Adverse Events (CTCAE) V.5.0.

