#### PROMs assessment

Changes in patient-reported health-related quality of life (QoL)/PROMs will be assessed using the following validated questionnaires: Expanded Prostate Cancer Index Composite-26 (EPIC-26) (prostate cancer-related QoL and functional outcomes), European Organization for the Research and Treatment of Cancer Quality of Life Questionnaire (EORTC QLQ)-C30 (general QoL Score) and IPSS (urinary and sexual functional outcomes). The specific time points for these evaluations are:

Baseline assessment (prior to salvage treatment).1 month post-treatment completion.3 months post-treatment completion.6 months post-treatment completion.12 months post-treatment completion.24 months post-treatment completion.

The PROMs and quality-of-life assessments will not require a separate face-to-face meeting as these will be posted out to the participants. Follow-up after 2 years will be according to local policy.

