### Baseline and follow-up evaluation

Table 1 shows the full schedule of events.

**Table 1 T1:** Reirradiation options for previously irradiated prostate cancer schedule of events

Item\Time point	Baseline	During RT	1-month FU	3-month FU	6-month FU	12-month FU	18-month FU	24-month FU
Informed consent	x							
Registration	x							
Testosterone	x							
Confirmation of eligibility	x							
Randomisation to BT or SBRT	x							
Pretreatment prostate biopsy sample requested and stored	x							
Collection of clinical history and outcome data	x							x
Radiotherapy (BT or SBRT) details	x	x						
PSA test	x			x	x	x	x	x
Functional prostate mpMRI	x		x			x		
PROM assessment (EPIC-26, EORTC QLQ-C30 and IPSS)	x		x	x	x	x		x
Research blood test/urine	x		x	x	x			
Clinician reported adverse events		x	x	x	x	x	x	x

BT, brachytherapy; EBRT, external beam radiotherapy; EPIC-26, Expanded Prostate Cancer Index Composite-26; FU, follow-up; IPSS, International Prostate Symptom Score; mpMRI, multiparametric MRI; PROM, patient-recorded outcome measure; PSA, prostate specific antigen; EORTC QLQ, European Organization for the Research and Treatment of Cancer Quality of Life Questionnaire; RT, radiotherapy.

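### Where single-fraction HDR-BT is used, the 'During RT' clinician-toxicity column covers 1 day, against 9 to 14 days for SBRT and about 2 weeks for two-fraction HDR-BT, so it is not like for like

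*Protocol article*

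**What the plan says.** Under Toxicity assessment, the protocol article says that "Clinician reported treatment toxicity will be summarised at each time point as the proportion of patients experiencing each toxicity". The grade counted for each patient is the highest one under CTCAE. The article gives no look-back period.

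In Table 1 (Baseline and follow-up evaluation), the row "Clinician reported adverse events" is marked at seven time points: 'During RT', then 1, 3, 6, 12, 18 and 24 months. 'During RT' has no stated length.

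The length follows from the Interventions section:

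- HDR-BT is "either a single fraction 19 Gy treatment or 27 Gy in two fractions approximately 2 weeks apart", and which of the two "will be used to be decided by treating centre".
- SBRT is five fractions "delivered alternate days over no more than 2 weeks to provide a total dose of 36.25 Gy".

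Later visits are counted from the end of treatment for the questionnaires: "1 month post-treatment completion.3 months post-treatment completion" (PROMs assessment). No anchor is stated for the clinician visits, which carry the same labels in Table 1.

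**The concern.** A proportion by maximum grade depends on how long patients are observed. If one group is observed for a day and another for up to two weeks, the second will show more events even when the treatments are equally toxic. A reaction that starts 7 days after first irradiation falls under 'During RT' for an SBRT patient. For a single-fraction HDR-BT patient it can appear only at the 1-month visit.

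The Introduction gives a description of the two toxicity profiles, to support treatment choice, as a reason for the trial. Readers will therefore compare the columns across arms although no test is planned. Table 1 has no questionnaire during treatment, so the clinician record is the only toxicity record listed for that period.

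The centre chooses the HDR-BT schedule and randomisation is stratified by site. Comparing arms within a site therefore does not remove the imbalance at a single-fraction site. The pooled HDR-BT figure also depends on which centres recruit.

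**Working it through.** **Window lengths, from the stated schedules (calendar days, inclusive)**

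- Check on the SBRT schedule: 5 × 7.25 = 36.25 Gy, which agrees with the article.
- SBRT: strict alternate days 1, 3, 5, 7 and 9 give 9 days. Weekday-only delivery gives 10 to 12 days. The stated limit is 14 days.
- Single-fraction HDR-BT: 1 day.
- Two-fraction HDR-BT: a 14-day gap gives about 14 + 1 = 15 days.

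**Effect on the 'During RT' column when true toxicity is equal**

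The article gives no toxicity rate or onset pattern, so both are assumed. Take a constant onset rate h, the same in both arms, with a proportion p having an onset by day 30 from first fraction:

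h = -ln(1 - p)/30; proportion in a window of D days = 1 - exp(-hD).

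For p = 40%, h = 0.5108/30 = 0.01703 per day:

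| Schedule | D | 'During RT' |
|---|---|---|
| Single-fraction HDR-BT | 1 | 1.7% |
| SBRT, shortest | 9 | 14.2% |
| SBRT, longest | 14 | 21.2% |
| Two-fraction HDR-BT | 15 | 22.5% |

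The HDR-BT arm figure is s × 1.7% + (1 - s) × 22.5%, where s is the share of HDR-BT patients treated with one fraction. The article does not give s. SBRT minus HDR-BT, in percentage points:

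| s | HDR-BT arm | Gap (SBRT 9 to 14 days) |
|---|---|---|
| 1 | 1.7% | +12.5 to +19.5 |
| 2/3 | 8.6% | +5.6 to +12.6 |
| 1/3 | 15.6% | -1.4 to +5.6 |
| 0 | 22.5% | -8.3 to -1.3 |

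With s = 1, the gap is +5.7 to +9.1 points at p = 20% and +21.0 to +31.8 points at p = 60%.

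A different onset pattern gives different figures. If 30% of patients have an onset spread evenly over the first 14 days, the column reads 30% × 1/14 = 2.1% for single-fraction HDR-BT, 30% × 9/14 = 19.3% up to 30% for SBRT, and 30% for two-fraction HDR-BT. If every onset fell on day 1, or every onset came after day 15, there would be no gap.

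For scale, the 95% half-width for a difference between two arms of 30 at a 20% rate is 1.96 × √(2 × 0.2 × 0.8/30) = 20 points.

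**The 1-month column**

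If clinician visits run from treatment completion, as stated for the questionnaires, the 1-month visit (30 days) falls on about day 31 for single-fraction HDR-BT, day 39 to 44 for SBRT and day 45 for two-fraction HDR-BT. The interval after completion is equal, but the time since first fraction is not. Merging 'During RT' with the 1-month visit would not equalise the arms. If the same constant rate (p = 40%) continued, the merged figures would be 41.0%, 48.5% to 52.7%, and 53.5%. By 3 months, a shift of 8 to 14 days in time since first fraction matters little.

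**The case against.** **The sign and size of an arm difference are unknown.** This stands. A reader might infer that the table must show an early advantage for HDR-BT. The documents do not support that. Two-fraction HDR-BT has about the same window as SBRT or a slightly longer one, and the split of schedules is not given. If every centre used two fractions, the gap would be small or reversed. The rates and onset patterns above are assumptions.

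**'Time point' may mean status on the assessment day, and the look-back period may be set elsewhere.** The full protocol, case report form or SAP may define it, and onset dates may already be collected. This stands in part. Even on the status reading, however, single-fraction patients would be assessed on day 1 and SBRT patients up to day 14, so the column would still not be like for like.

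**Little depends on the column.** This largely stands. It is one of seven columns of a secondary outcome, the analysis is descriptive, and the article says that the study is not powered for differences between arms. A reader might also infer that the distortion carries into the toxicity rates behind the sample size. It does not: the Sample size section ties those rates to the key secondary endpoint, which is patient-reported, has no 'During RT' assessment and groups acute toxicity over 0 to 3 months. Future work describes a later trial of reirradiation against ADT alone with survival endpoints.

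**A common window does not equalise ascertainment.** This stands as a limit on the remedy. Table 1 gives single-fraction patients no clinician assessment between the treatment day and the 1-month visit.

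**Conclusion.** The point holds where single-fraction HDR-BT is used. The stated rule, applied to the stated schedules, produces a 'During RT' column that compares 1 day with 9 to 14 days (SBRT) or about 15 days (two-fraction HDR-BT). Nothing in the article equalises this. The 1-month column is affected to a lesser degree, on the assumption that clinician visits run from treatment completion.

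The window lengths follow from the text. The effect on the arms does not. At an assumed 40% onset by day 30 at a constant rate, the artefact ranges from about -8 to +20 points. At its upper end it is about as large as the sampling uncertainty for two arms of 30. Unlike sampling error, it would not shrink in a larger trial that used the same table.

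Visits from 3 months on and the key secondary endpoint are not materially affected. This is a reporting weakness that is worth correcting and easy to correct. It does not threaten the trial's feasibility aims.

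**What to change.** In Toxicity assessment, define the early clinician-reported summary as the maximum CTCAE grade among events with onset from first fraction to a common point counted from first fraction in both arms, for example 0 to 90 days. This matches the 0 to 3 month acute period that the article already uses for patient-reported toxicity. Counting 3 × 30 = 90 days from completion, the 3-month visit falls on about day 91 for single-fraction HDR-BT, day 99 to 104 for SBRT and day 105 for two-fraction HDR-BT, so it covers the window for every schedule. A 6-week (42-day) window would not even reach the 1-month visit of two-fraction HDR-BT (about day 45) or of SBRT at its 14-day limit (about day 44).

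Assign events to the window by onset date. Keep the later visits as planned. Show 'During RT' only as a description within each schedule (single-fraction HDR-BT, two-fraction HDR-BT, SBRT), not as an arm-level rate.

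The cost is a sentence or two in the toxicity summary, the use of onset dates, and slightly less timing detail in the headline table. Early events in single-fraction patients may be recalled at the 1-month visit rather than recorded on treatment, and the report should say so. No dose, schedule or visit changes.

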#### Secondary outcomes

Incidence of patient-reported acute (0–3 months) and long-term toxicity (>3 months) and impact on QoL determined by EPIC-26 (prostate cancer related QoL and functional outcomes), EORTC QLQ-C30 (general QoL score) and IPSS (urinary and sexual functional outcomes) measurements (key secondary endpoint).Incidence of clinician-reported treatment toxicity as per CTCAE V.5.0.Other feasibility endpoints include screening log summaries, treatment and questionnaire compliance, withdrawal rate and reasons for non-recruitment.

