### Sample size

This is an exploratory feasibility study, and there is no informative data in the published literature on which to base a sample size calculation. Therefore, a formal statistical power calculation has not been performed. Feasibility studies are not usually sufficiently powered to provide estimates of effect size, but instead aim to determine the feasibility of specific study aspects and to enable estimation of sample size parameters to inform future studies. For this feasibility study, we plan to recruit 60 patients in total (ie, 30 to each treatment arm) from three UK hospitals (Leeds Cancer Centre, The Christie and Mount Vernon Cancer Centre), all of which are high-volume tertiary prostate cancer treatment centres. This sample size has been informed by the National Institute of Health Research guidance on feasibility sample sizes and the toxicity outcome data from a recent systematic review.^13 24^ Few studies have evaluated PROMs feasibility, establishing the need for this trial.^25^ It is estimated that this number of participants will provide an adequate sample to estimate the toxicity rates for the key secondary endpoint in each arm (ie, 30 per arm).^26 27^ Recruiting 60 patients over 2 years, across 3 centres, would mean an average recruitment rate of 1 patient per centre per month. This information, combined with the estimated toxicity rates from the study, will be used to determine feasibility of a subsequent larger scale RCT.

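### No clinician CTCAE grading is scheduled before salvage treatment, so persisting effects of the first radiotherapy cannot be reliably separated from new toxicity

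*Protocol article*

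**What the plan says.** **Summary measure.** Under Toxicity assessment, clinician-reported toxicity is to be "summarised at each time point as the proportion of patients experiencing each toxicity, summarised by maximum grade experienced", on CTCAE V.5.0. The section mentions no baseline grade, no change from baseline and no rule for symptoms already present.

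**Schedule.** Table 1, under Baseline and follow-up evaluation, is introduced as the complete schedule. Its row "Clinician reported adverse events" is blank at baseline and marked in the other seven columns. The baseline visit does include "Collection of clinical history and outcome data", but the article does not say that this involves CTCAE grading.

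**Population.** Eligibility criteria requires "histologically confirmed locally recurrent prostate cancer (following previous radiotherapy no less than 2 years ago". The only entry limit on existing pelvic symptoms is urinary: "reasonable urinary function (International Prostate Symptom Score (IPSS)<20 and Qmax>10 mL/s on flow tests". Inflammatory bowel disease is excluded, but no criterion limits residual rectal or sexual effects of the first radiotherapy.

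**Endpoints.** Secondary outcomes lists "Incidence of clinician-reported treatment toxicity as per CTCAE V.5.0" separately from the patient-reported toxicity item, and only the latter is labelled key. The patient-reported questionnaires do have a "Baseline assessment (prior to salvage treatment" time point and are assessed as changes (PROMs assessment).

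**The concern.** Everyone in this trial enters with a previously irradiated prostate. Late urinary, bowel and sexual effects of that treatment are a plausible background, and a stable symptom can be present at every follow-up visit. If the grade before salvage is not recorded, a grade 1 or 2 finding at 6 months may be new, worse, unchanged or even improved, and the raw maximum grade does not show which.

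At stake are the absolute per-arm rates. The study is descriptive, so those rates are its main toxicity output. Randomisation balances pre-existing symptoms on average between the arms but does not remove an upward shift common to both. The gap also lies in data collection: an analysis plan can define worsening, but it cannot supply a pre-treatment grade that nobody recorded.

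**Working it through.** **Step 1: is the blank cell real?** Table 1 was read from a PDF, so its column alignment was checked against the text.

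| Row | Marks in Table 1 | Text elsewhere | Agree? |
|---|---|---|---|
| PROMs | Baseline, 1, 3, 6, 12, 24 months | Same six points (PROMs assessment) | Yes |
| Functional MRI | Baseline, 1, 12 months | Baseline, 1 month, 1 year (Translational MRI assessment) | Yes |
| Clinician-reported events | During RT, 1, 3, 6, 12, 18, 24 months | None to compare | – |

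The two rows that can be checked are aligned, so the empty baseline cell in the third is credible.

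**Step 2: which endpoint is affected?** The patient-reported endpoint has a pre-salvage measurement and is analysed as change. The clinician-reported endpoint has neither. The gap is confined to the latter.

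**Step 3: how large could the effect be?** The article gives no rate to reproduce, so this step is an illustration on assumed values. Let p be the true rate of a given new toxicity and b the prevalence of the same toxicity persisting from before. Assume that the two are independent and that the clinician makes no attribution. Then:

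- apparent rate = 1 − (1 − p)(1 − b)
- excess = b(1 − p)

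| b (assumed) | Apparent rate if p = 10% | Apparent rate if p = 20% |
|---|---|---|
| 5% | 14.5% | 24% |
| 10% | 19% | 28% |
| 20% | 28% | 36% |
| 30% | 37% | 44% |

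For example, with p = 20% and b = 30%: 1 − 0.80 × 0.70 = 0.44. With 30 patients per arm (Sample size), that is 30 × 0.44 = 13.2 patients counted against 30 × 0.20 = 6 with new toxicity. At b = 5% it is 30 × 0.24 = 7.2 against 6. With both p and b between 5% and 30%, the excess runs from 0.05 × 0.70 = 3.5 points to 0.30 × 0.95 = 28.5 points.

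**Step 4: comparison with sampling error.** The 95% half-width for a 20% rate with n = 30 is 1.96 × √(0.20 × 0.80 / 30) = 14.3 points. With p = 20%, the excess is 4 points at b = 5%, 16 points at b = 20% and 24 points at b = 30%. It is therefore small beside the sampling error at low prevalence, and similar or larger from about 20% upward.

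**The case against.** **Clinicians may attribute.** The endpoint is worded as toxicity of treatment, and a clinician who knows the history may decline to record a long-standing symptom. A reader might infer that persisting effects will be counted as salvage toxicity; the article does not establish that. Attribution rules may also sit in the full protocol or case report form, and their absence from an article is no fault. This stands, and it limits the conclusion to possible bias. It does not replace a baseline grade, because case-by-case attribution at three sites may vary.

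**Baseline information exists.** Clinical history, EPIC-26, QLQ-C30 and IPSS are collected before treatment. They would help with interpretation and could reveal an imbalance between arms. None is stated to give a CTCAE grade by item, so they reduce the problem without closing it.

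**The link to the phase III decision.** Sample size says that recruitment information, "combined with the estimated toxicity rates from the study, will be used to determine feasibility of a subsequent larger scale RCT". A reader might take CTCAE incidence to be that input. The same section speaks just before of toxicity rates for the key secondary endpoint, and Secondary outcomes gives that label to the patient-reported item. CTCAE rates are at most supporting evidence for that decision.

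**The magnitudes.** No prevalence is given in the article, and the plan reports each toxicity by grade. A figure for any toxicity at all would not match a planned table, and prevalence for a single item at a given grade may be low. This stands: the range in the working applies item by item and only under its assumptions.

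**Between-arm comparison.** A reader might fear a spurious treatment difference. Allocation is randomised, Statistical analysis plans no hypothesis tests, and the strengths and limitations list says that the study is not powered to compare the arms. A chance imbalance remains possible, but this is not the main harm.

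**Conclusion.** The point holds in a limited form. The schedule omits a pre-salvage clinician grading in a population where everyone has been irradiated before, and the stated summary uses the raw maximum grade. The per-arm CTCAE rates may therefore overstate new toxicity, for one descriptive, non-key secondary endpoint.

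The amount is unknown. It rests on the persisting prevalence of each toxicity, on independence of old and new events, and on how far clinicians attribute. At a true new rate of 20% and with no attribution, the overstatement is 4 to 24 points for an assumed prevalence of 5% to 30%, and any attribution would shrink it. The documents do not support saying that the bias is certain, that it undermines the phase III decision, or that it favours either arm. This is a cheap improvement that can be made only before a participant starts salvage treatment.

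**What to change.** 1. In Table 1, mark the clinician-reported adverse events row at baseline and specify a CTCAE V.5.0 grading of existing symptoms at that visit, before salvage treatment.
2. Under Toxicity assessment, add that, for each toxicity and time point, the proportion with a new toxicity or a grade increased over baseline will be reported alongside the raw maximum grade.

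The cost is one extra case report form page at a visit that already takes place, one more set of summary columns and a sentence of analysis text. No visit is added and the sample size does not change. A baseline grade cannot be collected prospectively once treatment has begun, so the change is worth making early.
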